## Discussion

The current study emphasizes the need for cohort studies in China, especially in the BTH region, to understand NCDs and their risk factors. China is a very diverse country with different ethnic minorities, SESs, and rates of urbanization; thus, the risk factors for non-communicable conditions can vary widely from one geographical area to another. The prospective CKB, which includes more than 0.5 million adults, is the largest cohort in China. However, this cohort did not include a population in the BTH region. To our knowledge, the current study is the first large cohort study based on a community population in the BTH region. The current cohort is conducted in a centrally coordinated manner, which is similar to several cohort studies, such as LifeGene (33), National Health and Nutrition Examination Survey (34), and UK biobank (28). Central coordination center is located in Beijing and is composed of researchers from Capital Medical University and the Chinese Academy of Medical Sciences. The central coordination center is responsible for the quality control, training certification, biological sample storage, providing unified medical examination equipment, test center selection, participant recruitment, organizing CEC to ascertain outcomes, and proposing follow-up plan. Local CDC will assist in baseline field investigation and follow-up investigation.

China is a multiethnic country. There are 55 minorities in China in addition to the Chinese Han population. Most of the cohorts in China only contain the Han population. We will recruit not only a Chinese Han population in the cohort but also a Manchu population of ~10%. Manchu is one of the most populous minorities in the BTH region. Based on the sixth China national population census, Manchu was the largest minority group in Hebei (3.02%) (35). The Manchu population prefers sticky foods and a high-salt diet, and their prevalence of several diseases, such as hypertension and diabetes, is different from the Han population (36). Studies focusing on both Manchu and Han populations may help us to find more specific determinants of chronic disease in the BTH region. Moreover, the genetic background of the Manchu population is also different from that of the Han population (37). Given that population stratification will lead to spurious results and poor reproducibility in genetic association findings, grouping individuals into ethnic clusters will be effective in controlling population heterogeneity.

Classic cohort studies generally focus on certain types of exposure factors and certain types of diseases. The current cohort will not only focus on traditional lifestyle risk factors but also investigate dietary habits, mental health, environment, genetics, and epigenetics so that the etiology of common chronic diseases can be demonstrated comprehensively. Given that many chronic diseases share common pathogenic pathways, the current cohort will systematically analyze multiple exposures and their effects on diseases based on genomics, proteomics, and metabolomics to identify the specific and shared pathways of related diseases. For data collection, in addition to those based on previous traditional chronic disease management modes, this project will explore new methods to achieve real-time dynamic data monitoring and automatic data collection. For example, we will use an ID card reader to collect the subject's ID number, sex, birthday, and living address automatically and save the above information in an Excel table. The participants will be identified by the patient's ID number from the health management records in community healthcare centers, and their medical information will be collected and updated dynamically. Electronic information acquisition systems based on mobile terminals will play important roles not only in obtaining health-related big data but also in health management in the community. Moreover, 20% of the participants will be repeatedly measured in the follow-up visits, which offers an opportunity to conduct trajectory analyses to determine the dynamic patterns of risk factors contributing to the disease.

There are several limitations of the current cohort. First, the survey sites and the participants will not be randomly chosen. This is because the current study focuses on selected survey sites with various economic, medical, and environmental characteristics to better demonstrate the pathogenic mechanism of NCDs. In the central functional district of Beijing, we selected Chaoyang district. Tianjin and Shijiazhuang are in good terms of social economics with moderate air pollution, while Baoding is a city with moderate economic status and severe air pollution. Chengde city was selected as having better air quality. Xiong'an city may experience rapid economic development in the next 5 years. The residents' socioeconomic level and lifestyle may undergo tremendous changes, which may have a certain impact on health. Moreover, instead of estimating the prevalence of diseases by representative sampling, this cohort study is more concerned about the proportion of participants who could be followed up. Thus, we chose stable communities and participants to ensure a good follow-up rate. During the study recruitment process, the investigator will explain that enrollment in the cohort requires continued follow-up. Subjects who actively choose to join the cohort may have a stronger willingness to participate compared with randomly chosen participants, which may avoid loss to follow-up. Second, the current cohort will exclude participants with major physical and mental disabilities and any who could not complete the survey even with the help of investigators. These exclusion criteria may lead to a “healthy cohort” effect, and the results of this cohort study will be more applicable to a healthier population and should be explained and extrapolated with caution. Third, most of the surveys will be conducted on workdays, and elderly people and retirees may prefer to participate compared with young people and employees, which may introduce selection bias. To reduce selection bias and better represent the target population, we will recruit participants considering their demographic structure according to the results of the sixth national census. Finally, the same examination equipment will be used for physical examination to ensure the comparability of measurements. Because of the limited quantity of equipment, it is not possible to carry out repeated measurements at the same time. Therefore, in this study, only 20% of the subjects were repeated measured in each time of follow-up. It was planned to complete repeated measurements of all the subjects after five rounds of follow-up. In order to overcome the shortage of partial repeated measurements, telephone interviews and medical records update will be conducted to all participants every 2 years to obtain the change of lifestyle behavior and other health determinants.

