### Study Design and Settings

The CoHort study on CHronic disease of Community Natural population in Beijing–Tianjin–Hebei region (CHCN-BTH) is a population-based prospective cohort study, which has been registered with the Chinese Clinical Trial Registry (ChiCTR1900024725).

The sample size was estimated using the Cox regression module in PASS-NCSS 11.0 software. The parameters are as follows: statistical power is 80%, significance level is 0.05, and the lowest event rate is 50 per 100,000 (cardiovascular morbidity is ~650 per 100,000, and mortality is ~250 per 100,000; lung cancer morbidity is ~70 per 100,000, and mortality is 50 per 100,000). The log hazard ratio (HR) of PM_2.5_ per 10 μg/m^3^ is ~0.25 (HR = 1.28), the standard deviation of PM_2.5_ (per 10 μg/m^3^) is 1.4, and the *R*^2^ of PM_2.5_ with other covariates was set to 0.2. The lowest sample size was 32,037 according to the calculation of PASS software. Thus, the cohort was designed to recruit 36,000 individuals living in Beijing, Tianjin, and Hebei provinces by expecting a 10% loss to follow-up. The survey sites are shown in Figure 1. The CTCH-BTH cohort will include 30,000 community-lived individuals and 6,000 participants who undergo routine physical examinations. Most of the participants in the baseline survey were of the Chinese Han population, and ~10% of the participants were of Manchu ethnicity.

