### Sampling Methods

The cohort study was established with a multistage, stratified cluster sampling method. The cities are first selected according to geographical region, SES, and medical service quality. In the first stage, three cities were chosen as survey sites located in the southern, central, and northern parts of Hebei Province. Beijing and Tianjin are also designated survey sites. Among the above survey sites, the severity of air pollution and economic status are significantly different from each other, which can reflect the state of the natural population in Hebei Province. In the second stage, we selected districts from urban cities and counties from rural areas. In the next stage, communities were selected from districts in urban areas, while townships were selected from counties in rural areas. The new district called Xiong'an, which previously contained three rural counties, has now integrated into one urban city. In the final stage, residents in the selected area will be invited to participate in the study considering the demographic structure of the sixth national census. These procedures can ensure the representation of the sampling. Finally, the selected survey sites included 41 communities, 36 townships, and 7 functional units in five cities. Details of the sampling are shown in Figure 2.

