**Figure 3 F3:**
[figure not shown]
Flowchart of the baseline survey in CHCN-BTH.

Suitable places for the field survey were selected after consideration of the space needed for the survey instruments and the waiting space needed for the survey subjects. For example, we selected community healthcare centers or temporarily requisitioned schools near community healthcare centers as survey places. Face-to-face interviews will be performed using a uniform questionnaire. To ensure the accuracy of the questionnaire information, all questionnaires will be verified by the inspectors. The questionnaire includes five sections: sociodemographic characteristics, familial and personal medical history, lifestyle behaviors (including drinking, smoking, physical exercise), pollutant exposure (passive smoking condition and air pollution exposure condition), and psychological conditions. Current smoking was defined as smoking at least one cigarette per day in the last 6 months. Former smoking was defined as smoking less than one cigarette per day for at least 6 months. Alcohol drinking was defined as accumulatively drinking wine/liqueur more than 250 g/year or drinking beer more than 5 L/year (24). Physical exercise was defined as participating in moderate or vigorous activity for at least 30 min each time and at least once per week. Information on psychological conditions was collected using the Depression, Anxiety and Stress Scale-21 (25, 26). The scale includes three subscales, and each subscale contains seven items. The details of the questionnaire are shown in Table 2.

**Table 2 T2:** Sections and topics of the questionnaire.

**Type of data**	**Components**
Sociodemographic characteristics	Sex, age, ethnicity
	Residence address
	Cellphone number
	Personal income, education, occupation
	Menstrual history
Personal and family disease history	Hypertension (date of diagnosis, medication)
	Diabetes (date of diagnosis, medication)
	Cardiovascular disease (date of diagnosis, medication)
	Respiratory disease
	Gastrointestinal disease
	Cancer
	Others
Lifestyle behaviors	Tobacco use and smoking
	Alcohol consumption
	Labor intensity
	Physical activity/frequency
Outdoor exposure	Outdoor activity/frequency
	Window opening frequency
	Protective measurements during smog:
	Stay indoors/mask wearing/usage of air purifier
Indoor air pollution exposure	Passive smoking
	Cooking fuel type, cooking frequency
	Cooking habits:
	Kitchen door opening/usage of smoke extractors

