To screen for biomarkers and genetic markers of NCDs, lasso regressions will be used first, and then mixed models will be used to demonstrate their effect size in the longitudinal data. Logistic regressions and generalized linear models will also be used to confirm the effect of potential risk factors on NCDs. To demonstrate a genetic susceptibility to NCDs, single-nucleotide polymorphism (SNP), lncRNA, and mRNA expression profiles will be detected using a microarray. SNPs associated with diseases will be explored by logistic regression, and haplotypes will be identified by using Plink software. Gene–gene and gene–environment interactions will be demonstrated by using generalized multifactor dimensionality reduction and the random forest (RF) method. Differentially expressed genes (DEGs) will be identified using the R software Limma package (29). The lncRNA–mRNA coexpression network will be constructed based on the expression level of DEGs using weighted gene coexpression network analysis (30, 31). MiRNAs targeted by both lncRNAs and mRNAs in the lncRNA–mRNA coexpression network will be predicted by miRDB, TarBase, and TargetScan. All of the ceRNA loops will be combined and transformed into an “lncRNA–miRNA–mRNA” ceRNA network using Cytoscape software (32).

To construct risk prediction models, lasso regression, smoothly clipped absolute deviation, RF, support vector machine, and decision tree will first be used to screen for predictors of NCDs. Then, predictors selected by machine learning methods will be used to construct different prediction models by the Cox regression model. The Cox regression model with the best discrimination and calibration will be selected as the risk prediction model.

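### Grouping by ethnicity cannot on its own control population stratification; ancestry differences within Han could still inflate SNP false positives

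*Protocol article*

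**What the plan says.** - **The risk and the remedy (Discussion, paragraph on ethnicity).** The article states that "population stratification will lead to spurious results and poor reproducibility in genetic association findings", and from this concludes that "grouping individuals into ethnic clusters will be effective in controlling population heterogeneity". The conclusion carries no qualification.
- **The contrast behind the clusters.** The same paragraph notes that "the genetic background of the Manchu population is also different from that of the Han population". It says nothing about genetic differences within Han.
- **Composition (Study Design and Settings).** "Most of the participants in the baseline survey were of the Chinese Han population, and ~10% of the participants were of Manchu ethnicity". Ethnicity is recorded as a questionnaire item: Table 2 lists "Sex, age, ethnicity" under sociodemographic characteristics.
- **Geography (Sampling Methods).** "three cities were chosen as survey sites located in the southern, central, and northern parts of Hebei Province", with Beijing and Tianjin as further sites. The same section says the sites differ markedly in air pollution and economic status.
- **The analysis (Statistical Plan).** "SNPs associated with diseases will be explored by logistic regression". No ancestry or site term, and no other control for stratification, is named there.

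**The concern.** The article identifies a bias, names one remedy and declares it effective. As stated, the remedy covers only part of the bias. Conditioning on a Han/Manchu label makes comparisons within each label, so it removes confounding by the label. Any ancestry gradient inside the Han group is untouched, and that group holds most of the sample and spans the whole region.

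Stratification bias needs two things together: allele frequencies that differ between subgroups, and disease rates that differ between the same subgroups. The sites were chosen for contrasts in pollution and economic status, so differing disease rates are plausible, although no site-specific rates are given. Where both conditions hold, SNPs that merely mark geography would be flagged as disease markers more often than the nominal rate. Because pollution also varies by site, the planned gene–environment work could be exposed too; that was not quantified here.

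**Working it through.** **What the article supplies.** It gives no figure for the SNP analysis: no within-Han allele-frequency difference, no disease rate by site, no number genotyped and no SNP significance threshold. There is thus no stated figure to reproduce. The 0.05 level in Study Design and Settings belongs to the PM2.5 sample size and is used below only as a nominal reference.

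**Inputs**
- Han participants: 0.90 × 36,000 = 32,400. This assumes that everyone other than the ~10% Manchu is Han and that all are genotyped, so it is an upper figure. The alternative of 5,000 genotyped is an assumption.
- Two equal hidden subgroups within Han (assumption).
- Disease prevalence 30% and 40% in the two subgroups (assumption).
- Fst from 0.00001 to 0.001 (assumption). For two equal subgroups, Fst = 0.25 × (p1 − p2)² / [p(1 − p)].

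**Step 1: imbalance between cases and controls (32,400 Han, 16,200 per subgroup).**
- Cases: 4,860 + 6,480 = 11,340. Share from subgroup 1: 4,860 / 11,340 = 0.4286.
- Controls: 11,340 + 9,720 = 21,060. Share from subgroup 1: 11,340 / 21,060 = 0.5385.
- Difference in shares: −0.1099; squared, 0.01208.

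**Step 2: inflation of the 1-df allelic test.** The expected squared bias in the case–control frequency difference, in units of p(1 − p), is 0.01208 × Fst / 0.25 = 0.0483 × Fst. The sampling variance in the same units is 1/(2 × 11,340) + 1/(2 × 21,060) = 0.0000678. Hence

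λ = 1 + (0.0483 / 0.0000678) × Fst ≈ 1 + 712 × Fst.

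With 5,000 genotyped, the multiplier falls to 712 × 5,000 / 32,400 ≈ 110.

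**Step 3: actual error rate at nominal 5%.** This is 2 × [1 − Φ(1.96 / √λ)]. For example, at Fst 0.001, λ = 1.712, 1.96 / 1.308 = 1.498, and the rate is 13.4%.

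| Fst (assumed) | λ, 32,400 | Error rate, 32,400 | λ, 5,000 | Error rate, 5,000 |
|---|---|---|---|---|
| 0 | 1.000 | 5.0% | 1.000 | 5.0% |
| 0.00001 | 1.007 | 5.1% | 1.001 | 5.0% |
| 0.0001 | 1.071 | 5.8% | 1.011 | 5.1% |
| 0.0003 | 1.214 | 7.5% | 1.033 | 5.4% |
| 0.001 | 1.712 | 13.4% | 1.110 | 6.3% |

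**Step 4: sensitivity.**
- Equal prevalence in the two subgroups: 5.0% at every Fst, no inflation.
- Prevalence 5% versus 10%, 32,400 Han: 5.1% to 11.9% over Fst 0.00001 to 0.001.
- At a threshold of 5 × 10⁻⁸ (assumed), with 32,400 Han and 30% versus 40%, false positives rise about 1.1-, 2.8-, 15- and 620-fold at Fst 0.00001, 0.0001, 0.0003 and 0.001. The absolute rate stays small: 620 × 5 × 10⁻⁸ ≈ 0.003% per SNP.

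**Step 5: simulation check.** For 20,000 null SNPs at Fst 0.0003, with 32,400 Han and 30% versus 40%, grouping as Han only gave 7.6% rejections (formula: 7.5%). Adjusting for the subgroup gave 4.7%, about two Monte Carlo standard errors (√(0.05 × 0.95 / 20,000) = 0.15 points) below 5%. The simulation knew subgroup membership exactly; principal components would have to estimate it.

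**The case against.** **It is a Discussion remark.** The sentence closes an argument for recruiting Manchu participants. It does not say that grouping is the only control. The article condenses a fuller plan and names no adjustment covariates for its additive, Cox, logistic or mixed models either. A reader might infer that the SNP models will be run with no ancestry adjustment; the article does not support that, and the absence of a principal-component term is not in itself a finding. What remains is that the one remedy named is said to be effective without qualification, and for structure within Han that is incorrect.

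**The harm is conditional.** A reader might infer that false associations will follow. The article reports no disease rates by site and no within-Han genetic differences, and without both there is no inflation. All participants come from one region, so the effect may be small. This stands and limits the claim.

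**Larger figures can be produced.** For a single null SNP with frequencies 0.30 and 0.35 in two Han subgroups, prevalence 20% and 30%, and 32,400 genotyped, case and control frequencies are 0.330 and 0.323, z = 1.57, and rejection at 5% is about 35%. That SNP is selected for a gap corresponding to an Fst of about 0.003, above the range used here. With prevalence 20% versus 22% the figure falls to 6.3%; keeping 20% versus 30% but genotyping 5,000, it falls to about 9.5%. It should not be read as the error rate across SNPs.

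**Conclusion.** The point holds in a limited form. Han/Manchu grouping is presented as effective against stratification, yet it removes only between-group differences. Any ancestry gradient within the Han majority stays uncontrolled and can raise SNP false positives if allele frequencies and disease rates both vary across sites.

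The effect could run from negligible to material: at most 6.3% instead of 5% with 5,000 genotyped, and up to 13.4% with 32,400, at the top of the assumed Fst range with 30% versus 40% prevalence. These figures rest on two equal subgroups and on Fst, prevalence and genotyping numbers that the article does not give. The article does not show that false findings will occur, nor that the full analysis plan omits ancestry adjustment. The change is worth making because the present wording tells the analyst that the problem is already solved.

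**What to change.** - **Discussion:** qualify the sentence to say that ethnic grouping removes differences between Han and Manchu but is not sufficient alone, because structure within each group may remain.
- **Statistical Plan:** state that SNP logistic models are fitted within ethnic group and adjust for principal components derived from the genotypes and for survey site, or that a mixed model with a genetic relationship matrix is used. Report the genomic inflation factor for each outcome. If the full plan already says this, one sentence in the article is enough.

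**Cost:** routine computation on the planned microarray data, with no new data collection, provided the array's SNP coverage is broad enough to estimate ancestry. The article does not describe the coverage, so this should be confirmed first.

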
## Conclusion

The CHCN-BTH cohort will be a combination of self-reported data, medical records, and biological information. These data will contribute to our knowledge of risk factors for major NCDs and their survivorship. The survey sites of the CHCN-BTH cohort will have different socioeconomic and environmental statuses, and their socioeconomic and environmental status have experienced dramatic changes in recent decades. Significant spatial and temporal differentiation is well-suited to demonstrate the health determinants of NCDs in the BTH region, which will feed into public health strategies with regard to disease prevention and survivorship-related aspects.

## Ethics Statement

The studies involving human participants were reviewed and approved by Center for Disease Control and Prevention (CYCDPCIRB-20170830-1, Beijing, China; IRB2017-003, Hebei, China) Capital Medical University (2018SY81, China). The patients/participants provided their written informed consent to participate in this study.
